## Background {6a and 6b}

Gastrointestinal endoscopy is widely used for the diagnosis and treatment of digestive diseases. Midazolam and propofol are commonly utilized for procedural sedation during upper gastrointestinal endoscopy procedures [1]. Although both propofol and midazolam have demonstrated efficacy, they present specific limitations. Propofol provides desirable sedation depth and a short half-life (t1/2), enabling rapid patient recovery. However, it may cause respiratory depression, hypoxemia, and hypotension, necessitating continuous vital sign monitoring, including respiration. Midazolam, widely used, allows for easier sedation level titration compared to propofol, requiring less intensive monitoring. Its drawback is a half-life of 1–3 h [2, 3]. Remimazolam, a novel sedative and ester-based benzodiazepine, is rapidly hydrolyzed by liver esterase into its inactive carboxylic acid metabolite. With a shorter half-life than midazolam, remimazolam exhibits improved safety, facilitating swift awakening and early cognitive function restoration [4]. Phase III clinical trials of remimazolam for upper gastrointestinal endoscopy have demonstrated sedative effects and safety profiles in ASA grade (Appendix 1) I–II patients that are not inferior to propofol, with the sedative regimen outperforming propofol in certain aspects [5]. Procedural sedation safety and efficacy are primarily influenced by the patient’s physical condition. As ASA levels rise, the risk of adverse events during endoscopy increases [6]. Considering the requirements of upper gastrointestinal endoscopy, a safe and comfortable diagnostic and treatment experience during upper gastrointestinal endoscopy for these patients is important.

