#### Exclusion criteria

Subjects will be excluded if they meet one of the following criteria: (1) Patients who decline sedation and anesthesia; (2) history of drug abuse and/or alcoholism within the past 2 years; (3) patients who have taken monoamine oxidase inhibitors or cytochrome P450 inhibitors within the last month; (4) patients with known allergies to benzodiazepines, opioids, propofol, or lidocaine, or contraindications for receiving the aforementioned drugs; (5) participation in other clinical drug trials within 3 months prior to the start of the study; (6) pregnant or lactating women.

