### Randomization and allocation concealment {16}

The randomization method employs variable block randomization with random-sized blocks. Professional statisticians not involved in data management utilize the Data Web data collection management system to generate a central random sequence, randomly allocating subjects in a 1:1 ratio and dividing them into two groups. Stratification is based on whether upper gastrointestinal endoscopic invasive treatment is planned, as this factor may influence the duration of the procedure and potentially affect the sedation success rate. Random numbers are placed in coded, opaque envelopes and entrusted to personnel not involved in anesthesia or data collection for management.

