### Data Collection {18a}

#### Preoperative data collection

The baseline data collection will be conducted when the subjects enter the gastroscopy treatment room and are in a calm state. Upon obtaining informed consent from the subjects, the preoperative interviewer shall complete the baseline data collection as follows:

Demographic information, including name, gender, date of birth, height, and weightPreoperative diagnosis, including comorbidities (such as coronary heart disease, history of cerebrovascular accidents, hypertension, diabetes, chronic obstructive pulmonary disease, abnormal liver and kidney function), medication history (ACE inhibitors, ARBs, β-blockers, insulin, metformin, aspirin, clopidogrel, salbutamol, aminophylline, ipratropium bromide, etc.), smoking and smoking cessation history, and history of anesthesia and sedation.Severity of the disease or physical condition, ASA classification (refer to Appendix 1, with a requirement for participants to be classified as ASA III–IV).Baseline values of NIBP, HR, and SpO_2_ before the examination.Upper gastrointestinal endoscopy examination and planned examination location (esophagus and/or stomach).

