#### Efficacy evaluation{20a}

Primary endpoint evaluation: In the intention-to-treat (ITT) analysis population, a chi-square test will be used to compare the success rates of patients completing endoscopic examination and treatment between the two groups. Simultaneously, a generalized linear model will be employed to calculate the unadjusted and adjusted absolute risk differences (ARD). Adjusted variables will encompass stratification indicators (invasive procedures during upper gastrointestinal endoscopy and treatment), BMI, age, concurrent respiratory diseases, concurrent cardiovascular and cerebrovascular diseases, liver and kidney function abnormalities, and operator experience. Secondary effect sizes will be presented as odds ratios (OR) with a 95% confidence interval.

Evaluation of secondary endpoints: For the intention to treat (ITT, includes all participants who were randomly assigned, regardless of whether they completed the entire study or fully adhered to the study protocol) population, chi-square test or *t*-test will be employed for comparative analysis based on variable nature (e.g., categorical variables like low oxygen saturation, hypotension, tachycardia, intraoperative awareness, recovery delay, or continuous variables such as MOAA/S, NIBP, HR, and SpO_2_). Results will be reported as odds ratios (OR) and 95% confidence intervals using a generalized linear model. Time event variables (e.g., time to achieve a MOAA/S score of ≤ 3 points after a single dose) will be analyzed using Cox regression to describe and compare the two groups, generate Kaplan-Meier curves, express results as hazard ratios (HR), and report a 95% confidence interval.

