#### Exploratory analysis {20b}

Subgroup analyses based on patients’ clinical characteristics will be performed in pre-specified post hoc exploratory analyses. Potential factors impacting the examination success rate include BMI, age, the presence of respiratory diseases, cardiovascular and cerebrovascular diseases, liver and kidney dysfunction, alcohol and drug dependence, and operator experience.

Repeated measurement data (e.g., multiple measurements of MOAA/S, NIBP, HR, and SpO_2_) will be analyzed using a generalized additive mixed model (GAMM). The fixed effect will be a stratification indicator (invasive procedures during upper gastrointestinal endoscopy and treatment), and the interaction between groups and time will be evaluated.

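### The adjusted risk-difference model omits baseline SBP, HR, SpO2 and ASA grade, all of which are collected: a forgone precision gain, not an error; its stratum covariate should be tied to planned treatment

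*Protocol article*

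**What the plan says.** The section Efficacy evaluation {20a} plans a chi-square test in the ITT population and, alongside it, "a generalized linear model will be employed to calculate the unadjusted and adjusted absolute risk differences (ARD"). The adjustment set is spelled out: "Adjusted variables will encompass stratification indicators (invasive procedures during upper gastrointestinal endoscopy and treatment), BMI, age, concurrent respiratory diseases", followed by "concurrent cardiovascular and cerebrovascular diseases, liver and kidney function abnormalities, and operator experience".

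Four other places bear on that list.

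- **Preoperative data collection.** ASA classification is recorded, and so are "Baseline values of NIBP, HR, and" SpO2.
- **Primary outcome.** A patient fails if, during the examination, SpO2 falls below 90%, SBP is below 80 or at least 180 mmHg, or HR is 55 or less or above 100 per minute. Failure also follows if sedation depth is not reached before insertion or if inadequate sedation interrupts the procedure. The vital-sign limits are absolute values, not changes from baseline.
- **Background {6a and 6b}.** "As ASA levels rise, the risk of adverse events during endoscopy increases". The Discussion likewise treats ASA level as a predictor of perioperative risk.
- **Randomization and allocation concealment {16}.** "Stratification is based on whether upper gastrointestinal endoscopic invasive treatment is planned". Efficacy evaluation and Exploratory analysis both describe the stratification indicator instead as invasive procedures *during* endoscopy and treatment.

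Exploratory analysis {20b} lists subgroup factors ending in "alcohol and drug dependence, and operator experience", without ASA grade. The exclusion criteria rule out a "history of drug abuse and/or alcoholism within the past 2 years".

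**The concern.** The endpoint counts crossings of fixed SBP, HR and SpO2 limits, and the exclusion criteria set no bounds on those values at entry. A patient can therefore start close to a failure limit whichever drug is given. The baseline reading measures that directly; the listed comorbidities measure it only indirectly. ASA grade defines the trial population and is the risk marker on which the protocol builds its rationale, yet III versus IV is used nowhere in the analysis. The plan already runs an adjusted model, so leaving these variables out gives up precision that would need no new data. In a non-inferiority trial, precision determines how far the confidence limit sits from the 10% margin.

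The second matter is the stratum covariate. Both versions will exist in the data: the examination plan is noted at screening, and the procedures carried out are recorded afterwards. If an analyst used the performed procedure, the model would condition on something that happens after randomisation and might depend on how the sedation went. It would also not be the factor on which randomisation was stratified.

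**Working it through.** **1. Compare the lists.**

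| Variable | Collected at baseline | Tied to the endpoint or rationale | In adjusted model | In subgroup factors |
|---|---|---|---|---|
| SBP (from NIBP) | yes | endpoint limits <80, ≥180 mmHg | no | no |
| HR | yes | endpoint limits ≤55, >100 per minute | no | no |
| SpO2 | yes | endpoint limit <90% | no | no |
| ASA III/IV | yes | named as a risk predictor | no | no |

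**2. Reproduce the planned sample size.** Inputs from Sample-size calculation {14}: success 79% (taken as equal in both arms), margin 0.10, one-sided α 0.025, power 0.80, allocation 1:1.

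n per arm = (z₀.₉₇₅ + z₀.₈₀)² × 2p(1−p) / margin² = (1.960 + 0.842)² × 2 × 0.79 × 0.21 / 0.01 = 7.849 × 0.3318 / 0.01 = 260.4, so 261 per arm and 522 in total. This matches the stated 522. No covariate enters the calculation, so the sample size does not rely on adjustment.

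**3. Effect of extra prognostic covariates.** Let R² be the share of outcome variance that the four variables explain beyond the covariates already listed. The documents give no value; 0.02 to 0.10 is an assumption.

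SE = √[2p(1−p)(1−R²)/n], and power = Φ(0.10/SE − 1.96).

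At n = 261 and R² = 0: SE = √(0.3318/261) = 0.0357, and power = Φ(2.805 − 1.960) = 80.1%.

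| Assumed extra R² | SE ratio √(1−R²) | Power, 261 per arm | Power, 288 per arm | Total n for 80% power |
|---|---|---|---|---|
| 0 | 1.000 | 80.1% | 83.8% | 522 |
| 0.02 | 0.990 | 80.9% | 84.5% | 512 |
| 0.05 | 0.975 | 82.1% | 85.6% | 496 |
| 0.10 | 0.949 | 84.0% | 87.4% | 470 |

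The SE ratio is the result that applies to the planned adjusted model. The power columns start from the unadjusted calculation. The planned model would already exceed 80.1% if its listed covariates are prognostic, so these columns only illustrate the scale.

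**4. Check on the assumed range.** A simulation used 4,000 replicates, 261 per arm and 79% success, with a binary ASA IV term (15% prevalence assumed) and one standardised baseline predictor. Adjustment reduced the variance of the risk difference by about 2% for weak effects (log-odds 0.5 and 0.3), 5% for moderate effects (0.7 and 0.5), and 12–17% for strong ones (1.1 with 0.8 or 1.2). With no prognostic effect, power was about 80.3% either way, so adjustment cost nothing material. The simulation contains none of the already listed covariates, so its upper values overstate what would be extra here.

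**5. Stratum wording.** The randomisation section defines one stratification factor, fixed before allocation by what is planned. The analysis sections call the covariate a stratification indicator but describe it by what takes place during the procedure. The label points to the planned stratum; the parenthesis leaves the performed procedure open.

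**The case against.** The best case for the plan is that it contains no error here. Randomisation makes the unadjusted risk difference valid without any of these variables, the protocol reports that estimate, and the trial is sized on it. The listed comorbidities are sensible and may already carry part of what ASA grade and baseline vital signs would add. All of that stands, and it limits the point to efficiency.

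Four stronger readings are tempting, and the documents do not support them.

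- A reader might infer that the primary comparison is biased or invalid. It is not; omitting prognostic covariates does not bias a randomised risk difference.
- A reader might infer that ASA grade modifies the treatment effect. The protocol says only that risk rises with ASA level, which is prognosis. Nothing says that the difference between the drugs varies by grade.
- A reader might infer that the exclusion criteria abolish the alcohol and drug dependence subgroup. The exclusion reaches back only 2 years, so patients with an older history remain eligible. The subgroup is largely but not fully emptied, and it is exploratory.
- A reader might infer that the model will adjust for performed treatment. Because the covariate is called a stratification indicator, the planned stratum is the likelier intention. What remains is an ambiguity that one word removes.

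Nor can the move from 80.1% to 81–84% be read as the measured gain from the proposed change, because its starting point is the unadjusted analysis.

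**Conclusion.** The point holds as a recommendation of modest size. The enumerated adjustment set omits four collected baseline variables that the endpoint definition and the protocol's own rationale single out. The consequence is a forgone reduction of about 1–5% in the standard error of the adjusted risk difference. This rests on the assumption that the variables explain an extra 2–10% of outcome variance beyond the listed covariates, and the documents neither support nor contradict that range. The validity of the unadjusted result and the stated sample size are unaffected. The planned-versus-during wording is a small inconsistency and should be corrected in any case, because the less likely reading would put a post-randomisation variable into the model.

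**What to change.** 1. In Efficacy evaluation {20a}, add baseline SBP, HR, SpO2 and ASA grade (III/IV) to the covariates of the adjusted risk-difference model. SBP and HR have failure limits on both sides, so fix in advance how they enter; a straight-line term may miss risk at both ends.
2. In Efficacy evaluation {20a} and Exploratory analysis {20b}, state that the stratification covariate is the planned-treatment stratum used at randomisation, not the procedure performed.
3. As a minor exploratory change, add ASA III versus IV to the subgroup factors. If the alcohol and drug dependence factor is kept, note that only histories older than 2 years can contribute.

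The cost is wording in the protocol or the analysis plan. All the variables are already collected, and neither the sample size nor trial conduct changes. The changes should be fixed before outcome data are compared by arm.

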#### Secondary outcomes

*Sedation efficacy outcomes*: (1) MOAA/S score after single administration; (2) time required to achieve a MOAA/S score of ≤ 3 points following single administration; (3) for patients not achieving adequate sedation depth after a single dose and documentation of additional medication doses and frequency; (4) total amount and number of additional administrations of remimazolam or propofol in both groups during the entire course of upper gastrointestinal endoscopy and treatment; (5) duration from the initiation of medication injection to the completion of upper gastrointestinal endoscopy and treatment; (6) type, frequency, and dose of alternative or additional remedial drugs required when the upper limit of supplementary dosage is exceeded; and (7) operator satisfaction.

*Consciousness recovery outcomes*: (1) Time to full awakening; (2) use of sedative antagonist flumazenil, if applicable; (3) assessment of patients’ recall of upper gastrointestinal endoscopy and treatment process using the Brice questionnaire (Appendix 4) after awakening; (4) duration of patients’ recovery; and (5) overall patient satisfaction.

*Safety outcomes*: (1) Incidence of hypertension or hypotension during the procedure and in the recovery room, (2) incidence of tachycardia or bradycardia during the procedure and in the recovery room, (3) incidence of low oxygen saturation during the procedure and in the recovery room, (4) airway intervention rate during the procedure and in the recovery room, (5) incidence of coughing within 1 min after endoscope insertion, (6) incidence of coughing during upper gastrointestinal endoscopy and treatment, and (7) incidence of injection-related pain.

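### The named secondary-endpoint tests leave out the randomisation stratum, so comparisons of stratum-related outcomes such as procedure duration can be conservative

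*Protocol article*

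**What the plan says.** Under Randomization and allocation concealment {16}, the protocol article describes variable blocks, "randomly allocating subjects in a 1:1 ratio and dividing them into two groups", and gives the reason for the stratum: "Stratification is based on whether upper gastrointestinal endoscopic invasive treatment is planned, as this factor may influence the duration of the procedure". The same sentence adds a possible effect on sedation success.

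Secondary outcomes, under sedation efficacy, include the "duration from the initiation of medication injection to the completion of upper gastrointestinal endoscopy and treatment" (item 5) and the amount and number of additional administrations (item 4).

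Efficacy evaluation {20a} sets the methods for secondary endpoints:

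- A "chi-square test or *t*-test will be employed for comparative analysis based on variable nature", with examples that include "continuous variables such as MOAA/S, NIBP, HR, and SpO_2".
- On effect estimates, the section states: "Results will be reported as odds ratios (OR) and 95% confidence intervals using a generalized linear model". No covariates are listed for this model.
- Time variables "will be analyzed using Cox regression to describe and compare the two groups". No strata or covariates are listed.

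The stratum is written in at two other places. In {20a} it heads the covariate list for the adjusted primary risk difference. In Exploratory analysis {20b} it enters the additive mixed model for repeated measurements: "The fixed effect will be a stratification indicator (invasive procedures during upper gastrointestinal endoscopy and treatment".

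**The concern.** The stratum was chosen partly because it may drive duration, yet the tests named for the secondary comparisons cannot use it. Stratified blocks keep the stratum balanced between arms, so between-stratum spread adds almost nothing to the true sampling error of the treatment difference. A two-sample t-test still counts that spread as random error, so its standard error is too large. For an outcome strongly related to the stratum, the 95% interval then covers more than 95% of the time, and the p<0.05 rule set under General principles {20a} rejects less often than 5% under the null. A real difference is easier to miss. The outcomes most exposed are duration, the number of additional administrations, and possibly recovery time.

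**Working it through.** **The plan's own figure.** The only sample-size figure concerns the primary endpoint. With 79% in both arms, margin 0.10, one-sided 0.025 and 80% power, n per arm = (1.960 + 0.842)² × 2 × 0.79 × 0.21 / 0.10² ≈ 260.4, so 261 per arm and 522 in total. Adding 10%: 261 × 1.1 = 287.1, so 288 per arm and 576 in total. Both stated figures reproduce, and neither bears on this point. No SD, power or interval width is given for any secondary endpoint.

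**Inputs that must be assumed.** Let q be the share with planned invasive treatment, and d the difference in mean outcome between strata in units of the within-stratum SD. The SD is taken as equal in both strata. The document gives neither q nor d.

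**Continuous outcomes.** With 1:1 allocation balanced within strata:

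- Ratio of unadjusted to stratum-adjusted interval width: w = √(1 + q(1−q)d²).
- Actual two-sided type I error of the unadjusted test: 2 × [1 − Φ(1.960w)].
- Power of the unadjusted test, for an effect at which the adjusted test has 80%: Φ(1.960 + 0.842 − 1.960w).

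Worked case, q = 0.3 and d = 1: w = √(1 + 0.21) = 1.10. Type I error = 2 × [1 − Φ(2.156)] = 0.031. Power = Φ(2.802 − 2.156) = Φ(0.646) = 74.1%.

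| q | d | w | Actual type I error | Unadjusted power (adjusted 80%) |
|---|---|---|---|---|
| 0.1 | 0.5 | 1.011 | 0.048 | 79.4% |
| 0.3 | 0.5 | 1.026 | 0.044 | 78.5% |
| 0.3 | 1 | 1.100 | 0.031 | 74.1% |
| 0.3 | 2 | 1.356 | 0.008 | 55.7% |
| 0.5 | 2 | 1.414 | 0.006 | 51.2% |

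**Simulation check.** This used 522 patients, permuted blocks of four within strata, normal outcomes and 4,000 replicates per scenario.

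| q | d | Width ratio | Type I error, unadjusted / adjusted | Power, unadjusted / adjusted |
|---|---|---|---|---|
| 0.1 | 0.5 | 1.011 | 0.047 / 0.049 | 78.7% / 79.3% |
| 0.3 | 1 | 1.10 | 0.035 / 0.051 | 74.3% / 80.2% |
| 0.5 | 2 | 1.42 | 0.004 / 0.051 | 49.9% / 79.4% |

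The formulas hold.

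**Binary outcomes (risk difference).** With stratum risks p₀ and p₁ and overall risk p̄, w = √{p̄(1−p̄) / [(1−q)p₀(1−p₀) + q·p₁(1−p₁)]}. For q = 0.5 and risks of 20% and 50%: p̄ = 0.35, the total variance is 0.2275, the within-stratum variance is 0.205, and w = 1.053. Over q from 0.1 to 0.5 and risk pairs from 10%/20% to 20%/50%, w runs from 1.005 to 1.053, and unadjusted power from 79.7% down to 76.9%.

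**The case against.** The strongest reply is that the article is silent on the stratum and does not exclude it. Secondary estimates come from a generalized linear model and a Cox model whose covariates are not listed, and a condensed article may leave such lists to a fuller plan. The t-test examples are MOAA/S, NIBP, HR and SpO₂, and repeated measurements of these also go to the mixed model that carries the stratum. Duration and drug use are not assigned to the t-test by name, and duration could fall under Cox regression. Nothing invalid results, and no power is claimed for any secondary endpoint.

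Part of this stands. The article does not establish that the reported odds and hazard ratios are unadjusted, and adjustment changes what those ratios estimate. So too wide is a clean description only for mean and risk differences.

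It does not remove the point. The two-sample t-test and chi-square test are stated methods with no place for a stratum. The t-test examples are illustrative, and the rule is to choose by type of variable. An odds ratio is not a usable summary of duration or a count of top-ups, and if duration goes to Cox regression, no stratum is stated there either. Where adjustment is intended, {20a} and {20b} say so.

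A reader might go further and infer that the duration and drug-use intervals are certainly too wide and that real differences in drug use will be missed. The document does not support this. It says only that the factor may influence duration, and it gives no stratum share or spread. Total milligrams are not a meaningful contrast between drugs started at 1.5 and 0.15 mg/kg.

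**Conclusion.** The point holds as a matter of efficiency in the secondary analyses. As written, the named tests ignore the randomisation stratum, and for continuous outcomes related to it the comparison is conservative. The size rests wholly on assumed values: negligible if the strata differ little, a moderate loss of about 6 points of power at 30% invasive and 1 SD, and a large loss of about 24 points at 2 SD. Binary outcomes lose little. Treatment differences in means or risks are not biased and type I error is not inflated. The primary non-inferiority analysis and its sample size are not affected, so the omission should not be read as a threat to the trial's main conclusion. It is worth correcting because the remedy is free and would bring the secondary analyses into line with the adjusted primary analysis and the mixed model.

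**What to change.** In Efficacy evaluation {20a}, state that secondary comparisons use models that include planned invasive treatment (yes/no) as randomised, and report the stratum-adjusted estimate with its 95% interval:

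- **Continuous outcomes** (duration, number of additional administrations, recovery time): linear regression on treatment and stratum, on the log scale where a positive outcome is skewed.
- **Binary outcomes:** Mantel-Haenszel, or logistic regression with the stratum.
- **Time-to-event outcomes:** Cox regression stratified by it.

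Name the method for duration and for additional administrations, since none is assigned now. The words as randomised matter because {20a} and {20b} describe the indicator as invasive procedures during endoscopy, whereas randomisation is stratified on what was planned.

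The cost is a change of wording and one degree of freedom in the regression models. The stratum is known for every randomised patient, so no patients, visits or data are added. The small downside is that odds and hazard ratios become conditional on the stratum, which the report should say.

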#### Intraoperative data collection

Starting from the administration of intervention drugs, test the MOAA/S score every 30 s for 5 min, and then test every 2 min until the examination and operation are completed.

Record the time interval (seconds) from the start of intervention drugs to the time when MOAA/S score ≤ 3.

Record the presence of injection pain during the administration of intervention drugs using a visual analog scale (VAS) ranging from 0 to 10, where 0 indicates no pain and 10 indicates maximum pain (see Appendix 3). This assessment is conducted 1 min and 20 min after the start of drug administration or every 5 min thereafter if the patient remains sedated until the patient can complete the scale.

Record the MOAA/S score when the endoscope is smoothly placed in the esophagus.

Record the dose of intervention drugs used when the endoscope is smoothly inserted into the esophagus (including additional and rescue drugs, types, frequency, and dosage).

Measure NIBP every 3 min from the start of intervention drugs until the end of the examination.

Continuously monitor SpO_2_ until the end of the examination and record the minimum SpO_2_ during the procedure.

Record the total duration of the examination and operation (in minutes).

Record the types, frequency, and dosage of additional or rescue drugs during the examination, along with the corresponding time points.

Record the number of interruptions during the examination and the reasons for interruption, along with the time elapsed since drug administration began.

Record adverse events and their corresponding times during the period from drug administration to the end of the examination (see 1.10), such as respiratory spasms, reflux aspiration, coughing during endoscope entry into the oral cavity, SpO_2_ below 90% due to repeated coughing, SpO_2_ below 90% due to respiratory depression, positive pressure mask ventilation, jaw support-assisted ventilation, systolic blood pressure < 80 mmHg, or the need for vasopressors, systolic blood pressure ≥ 180 mmHg, *HR* ≤ 55 beats/min, *HR* > 100 beats/min, and the frequency and conditions of severe arrhythmias.

Operator satisfaction score (0–10 points, with 0 indicating very dissatisfied and 10 indicating very satisfied).

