### Statistical analysis

#### General principles{20a}

Continuous variables will be represented as means (standard deviations) or medians (minimum, maximum, or interquartile range), with the Shapiro-Wilk test applied to evaluate the normality of continuous variable distributions. Categorical variables will be expressed as frequencies (percentages).

All statistical analyses will involve two-sided tests, considering a *p*-value less than 0.05 to be statistically significant.

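### The secondary analysis prescribes odds ratios for continuous MOAA/S, NIBP, HR and SpO2, which does not fit its own t-test, and the repeated-measures model for the same four variables is only exploratory

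*Protocol article*

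**What the plan says.** Three parts of the protocol article bear on this.

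- **Efficacy evaluation, secondary endpoints.** The test depends on the type of variable: "chi-square test or *t*-test will be employed for comparative analysis based on variable nature". The examples given for the continuous type run directly into the effect measure: "continuous variables such as MOAA/S, NIBP, HR, and SpO_2_). Results will be reported as odds ratios (OR"). The same sentence adds 95% confidence intervals from a generalized linear model. Only time-to-event variables get a different measure (hazard ratios from Cox regression).
- **Exploratory analysis.** "Repeated measurement data (e.g., multiple measurements of MOAA/S, NIBP, HR, and SpO_2_) will be analyzed using a generalized additive mixed model (GAMM"). The section names the stratification indicator as the fixed effect and adds an evaluation of the group-by-time interaction.
- **Intraoperative data collection.** For MOAA/S, the instruction is to "test the MOAA/S score every 30 s for 5 min, and then test every 2 min until the examination and operation are completed". For blood pressure: "Measure NIBP every 3 min from the start of intervention drugs until the end of the examination". The Recovery room section continues both series, at 5-minute and 3-minute intervals.

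General principles sets the error level: "All statistical analyses will involve two-sided tests, considering a *p*-value less than 0.05 to be statistically significant".

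**The concern.** Two statements do not fit together, and a third leaves a gap.

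First, the effect measure is wrong for the variables it covers. A t-test on blood pressure, heart rate or saturation asks whether two means differ. The matching estimate is a mean difference in mmHg, beats per minute or percentage points. An odds ratio needs a binary outcome or an ordinal model, and the plan states neither a cut-off nor such a model for these continuous variables. An analyst following the text would have to invent one, or report an estimate and a p-value that answer different questions.

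Second, the same four variables appear under two methods of different standing. The method that allows for several readings per patient is exploratory; the t-test, which does not, is secondary.

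Third, for NIBP and HR the plan does not define the value to which a t-test would apply. The listed safety outcomes for them are incidences, which are binary. What is collected after baseline is a series.

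At stake are the continuous comparisons of sedation depth and haemodynamics. The primary non-inferiority comparison is not touched.

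**Working it through.** **1. Effect measure, by outcome type as the plan states it**

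| Outcome type | Test named | Effect measure named | Do they match? |
|---|---|---|---|
| Categorical (e.g. hypotension, low saturation) | chi-square | odds ratio | yes |
| Continuous (MOAA/S, NIBP, HR, SpO2) | t-test | odds ratio | no: the t-test examines a mean difference |
| Time to event | Cox regression | hazard ratio | yes |

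This step needs no assumption.

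**2. Is there one value per patient for the t-test?**

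- MOAA/S: yes. The score after the single dose is a listed secondary outcome, and the score at endoscope placement is recorded.
- SpO2: yes. The minimum is recorded during the procedure and in recovery.
- NIBP and HR: baseline values only. After baseline, Secondary outcomes lists incidences of hypertension, hypotension, tachycardia and bradycardia, and Intraoperative data collection schedules an NIBP series. No continuous summary is defined.

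**3. What would follow if the series were pooled**

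The plan gives no figure on this point, so there is none to reproduce. Its sample size does reproduce: 2 × 0.79 × 0.21 × (1.96 + 0.84)² / 0.10² gives 261 per arm, 522 in total, and 261 × 1.1 rounds up to 288 per arm, 576 in total. It is not in dispute.

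Inputs: two-sided level 0.05 (General principles). The number of readings m and the within-patient correlation ρ are **assumptions**; the article gives neither. For scale, one MOAA/S reading every 30 s for 5 min is 5 × 60 / 30 = 10 readings.

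If all readings enter a t-test as independent, the variance is understated by the factor D = 1 + (m − 1)ρ, and the actual type I error is 2 × [1 − Φ(1.96 / √D)].

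| m | ρ | D | Type I error |
|---|---|---|---|
| 4 | 0.5 | 2.5 | 21.5% |
| 6 | 0.5 | 3.5 | 29.5% |
| 10 | 0.5 | 5.5 | 40.3% |
| 4 to 10 | 0.05 | 1.15 to 1.45 | about 7% to 10% |
| 4 to 10 | 0.7 | 3.1 to 7.3 | about 27% to 47% |

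A simulation with 261 patients per arm, m = 5, ρ = 0.5, no treatment effect and 4000 runs gave 26.4% for pooled readings (formula: D = 3.0, 25.8%). In the same runs, a t-test on one value per patient gave 4.9% (a single reading), 5.5% (the mean) and 5.8% (the minimum).

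The inflation therefore depends entirely on pooling. One value per patient removes it.

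**The case against.** A reader might infer that the plan counts correlated readings as independent and so inflates false positives. The documents do not support that. The t-test sentence only says that the test follows the type of variable and gives examples; it nowhere says that each reading is an observation. The next section gives the multiple measurements to a mixed model, which suggests that the authors separate single values from series. Single values exist for MOAA/S and SpO2. The listed haemodynamic safety outcomes are incidences, which can be analysed once per patient and go to the chi-square test. This part of the objection stands in full: the error rates above show what pooling would do, not what is planned.

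It can also be said that the choice of time point or summary is detail that an article leaves to the full protocol or analysis plan. That is fair, and the missing summary for NIBP and HR would not be a finding by itself. It matters here because the article names these variables for a t-test while listing no continuous outcome for them.

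Lastly, the odds-ratio sentence follows a mixed list and fits its categorical half, so it may be loose drafting. That may be so, but time-to-event variables are set apart and continuous ones are not. As written, the rule covers them, and this is something the plan states rather than omits.

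**Conclusion.** The point holds in limited form. On the text alone, the odds-ratio rule is wrong for continuous secondary outcomes and does not match the test named for them. The same four variables are also assigned to a secondary t-test and an exploratory mixed model, with no continuous outcome with one value per patient for NIBP or HR after baseline. None of this rests on an assumption.

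The risk to type I error is conditional: about 20% to 40% if 4 to 10 readings per patient were pooled at an assumed correlation of 0.5, and near 5% if each patient contributes one value. The plan does not state pooling, so inflated error is not a property of the plan. The matter should be corrected, but it concerns secondary analyses only.

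**What to change.** In Efficacy evaluation, secondary endpoints:

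1. Restrict the t-test to continuous outcomes with one value per patient, for example MOAA/S after the single dose, minimum SpO2 and the satisfaction scores. If a one-value comparison of NIBP or HR is wanted, define the summary under Secondary outcomes.
2. Name the mixed model already planned under Exploratory analysis as the secondary analysis of the MOAA/S, NIBP, HR and SpO2 series. State a patient random effect and a group term explicitly, beside the stratification indicator and the group-by-time interaction.
3. Report mean differences with 95% confidence intervals for continuous outcomes, odds ratios only for binary outcomes, and hazard ratios for time-to-event outcomes as now.

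The cost is wording. The model is already planned, no new data are needed and the sample size is unaffected. Confidence intervals for the series will be wider than pooled readings would give, because pooling would understate the uncertainty.
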